### Secondary outcomes

Saturated fat (g/MJ), energy content (kJ/MJ), and expenditure ($/MJ) on household food purchases will be assessed at the end of intervention (weeks five and six). Systolic blood pressure, ambulatory blood pressure (sub-study 1; n ~ 40), and urinary sodium of the household member with CVD, and use and acceptability of the SaltSwitch app (main household shopper) will be assessed at baseline (week 0) and end of intervention (week 6). With the exception of ambulatory blood pressure, all outcomes will be assessed over the longer-term, at weeks 11 and 12, in a sub-group of ~20 people with CVD (and their main household shopper where applicable) who remain enrolled in the study (sub-study 2). Serious adverse events (SAEs) will be recorded for the duration of the study.

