**The SaltSwitch smartphone application.**

A growing body of evidence indicates that mobile technology can support behaviour change [22], yet robust evidence for smartphone interventions is lacking. This manuscript outlines the rationale and methods for a randomized controlled trial designed to determine the effectiveness of SaltSwitch in supporting people with CVD to make lower-salt food choices. The primary hypothesis is that four weeks’ intervention with SaltSwitch will reduce the salt content of household food purchases compared with control. Secondary hypotheses are that four weeks’ intervention with SaltSwitch will reduce the saturated fat and energy content of household food purchases, and the systolic blood pressure and salt intakes (measured by urinary sodium excretion) of participants with CVD. The SPIRIT checklist for Standardised Protocol Items was followed in writing this manuscript [23] and the protocol described reflects the most recent version (Version 2 dated 12^th^ May 2014).

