**SaltSwitch trial design.**

### Aims

The primary aim is to determine the effect of the SaltSwitch smartphone app on the salt content of food purchases made by households where at least one member has diagnosed CVD. Secondary aims are to evaluate the effect of SaltSwitch on: (1) saturated fat and (2) energy content of food purchases made by households; and (3) systolic blood pressure and (4) urinary sodium of participants with CVD. Household food expenditure, and use and acceptability of the SaltSwitch app by shoppers will also be assessed. Ambulatory blood pressure of participants with CVD and potential longer-term impact (12 weeks) of SaltSwitch will be assessed in two sub-studies (n ~ 40 and n ~ 20, respectively).

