### Sample size

The target sample size of 300 participants with CVD (150 per group) will provide 80% power at 5% level of significance (two-sided) to detect a treatment difference of 0.07 g/MJ (~10%) of salt in household food purchases, between the two groups at follow up (average over weeks five and six) assuming a standard deviation of 0.22 g/MJ. The target sample size was estimated using data on baseline purchases of salt (mean (SD), 285 (88) mg/MJ) made by participants in a previous supermarket intervention trial (n = 1,104) in New Zealand [24] and estimated intervention effects from the Dietary Approaches to Stop Hypertension study [25].

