### Primary outcome

The primary outcome is the salt content of household food purchases (g/MJ) at the end of intervention (weeks five and six).

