### Measurement of study outcomes

Outcome measurements for participants with CVD are undertaken in clinics at one of two locations; either the University of Auckland, or Auckland Hospital. A research assistant telephones each participant to arrange a convenient time and venue of choice for baseline, week 6, and week 12 assessments (Figure 2). Main household shoppers who do not have CVD are also encouraged to attend. On arrival at the clinic, the researcher explains procedures, answers any questions, and collects consent forms (baseline only). Height, weight, blood pressure and a urine sample are collected, and participants self-complete two on-line questionnaires. Main household shoppers who are present at clinic appointments also self-complete baseline and follow-up questionnaires; those not present are sent a link to their questionnaire in an email.

Primary outcome: the salt content of household food purchases will be assessed using supermarket till receipts linked to brand-specific food and nutrient information from the SaltSwitch app (see Intervention section). Main household shoppers are provided with a receipt collection box and return address, postage paid envelopes to return all till receipts for household food and beverages purchased during the trial. All till receipts are photographed and uploaded to a bespoke web-based data entry system that stores data on all purchased foods and beverages and their costs. The number of purchased items not included in the SaltSwitch food and nutrient database will be recorded and included in analyses.

Secondary outcomes: the saturated fat and energy content of household food purchases, and expenditure on food, will be assessed using data from till receipts, as described for the primary outcome.

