### Statistical analyses

Statistical analyses will be performed using SAS version 9.3 (SAS Institute Inc. Cary NC, USA). All statistical tests will be two-sided and a 5% significance level maintained throughout the analyses. Baseline characteristics will be summarised using descriptive statistics by treatment groups and overall. Continuous variables will be described as numbers of observed values, mean ± standard deviation. Categorical variables will be described as numbers and percentages. Since any differences between randomised groups at baseline could only have occurred by chance, no formal significance testing will be conducted.

Treatment evaluation will be performed on the principle of intention-to-treat (ITT), using data collected from all randomised participants. Missing outcome data will not be imputed, as it is difficult to make assumptions about the missingness of supermarket till receipt data, or the direction of the imputed values. Those randomised participants who are considered compliant to the study protocol will be included in a secondary per protocol (PP) analysis. Those households with at least three shopping episodes during the 4-week intervention period (seven or more shopping episodes during the 12-week intervention period for sub-study 2), with a total weekly spend of $25 or more per person, will be considered compliant. Analysis of covariance (ANCOVA) regression models will be used to evaluate the main treatment effect on the primary outcome, adjusting for baseline outcome measures; ethnicity, age, and gender. Model-adjusted means and their difference between the two treatment groups will be estimated and tested. A similar approach will be used for other continuous secondary outcomes, measured at the end of intervention period. Generalized linear models will be applied to categorical outcomes as appropriate. A pre-specified statistical analysis plan outlines all planned analyses and statistical methods.

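### The secondary outcome for energy is given in kJ/MJ, which is 1000 for every household, so as printed it cannot test the energy hypothesis

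*Protocol article*

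**What the plan says.** The protocol article scales purchases by the energy they contain. For salt: "The primary outcome is the salt content of household food purchases (g/MJ) at the end of intervention (weeks five and six". The Secondary outcomes section uses the same denominator for three further quantities: "Saturated fat (g/MJ), energy content (kJ/MJ), and expenditure ($/MJ) on household food purchases will be assessed at the end of intervention".

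Energy is a named target of the trial. The hypotheses at the end of the Background say that four weeks with the app "will reduce the saturated fat and energy content of household food purchases", and the Aims list "1) saturated fat and (2) energy content of food purchases made by households".

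Under Measurement of study outcomes, the source is the same set of receipts as for salt: "the saturated fat and energy content of household food purchases, and expenditure on food, will be assessed using data from till receipts". Neither that section nor any other gives a second unit for energy, such as per 100 g, per person, per day or per dollar.

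For the analysis, the primary outcome gets an ANCOVA adjusted for its baseline value, ethnicity, age and gender, and then: "A similar approach will be used for other continuous secondary outcomes, measured at the end of intervention period".

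**The concern.** A per-MJ scale suits salt, saturated fat and money because the numerator is a mass or a cost. Applied to energy, it puts the same quantity above and below the line. What remains is a conversion factor and not a measurement.

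At stake is one of four secondary hypotheses (saturated fat, energy, systolic blood pressure, and salt intake measured by urinary sodium). Sub-study 2 is affected too, because it repeats every outcome except ambulatory blood pressure at weeks 11 and 12.

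The intended unit cannot be recovered from the text. Energy density describes the composition of what is bought; total energy per person describes how much is bought. If the choice stays open, it could be made after the data have been seen.

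**Working it through.** **Inputs.** The unit kJ/MJ (Secondary outcomes); the per-MJ convention (Primary outcome); till receipts as the single source (Measurement of study outcomes); baseline-adjusted ANCOVA (Statistical analyses). The plan states no expected mean, SD or effect for energy, so there is no figure of its own to reproduce for this outcome.

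**Step 1: the value of the outcome.** Let a household's purchases in a period contain E kJ, with E > 0. The same purchases contain E/1000 MJ. The outcome is

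E / (E/1000) = 1000 kJ/MJ.

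E cancels. With an illustrative total of 150,000 kJ, the outcome is 150,000/150 = 1000. If the household halves its purchases to 75,000 kJ, it is 75,000/75 = 1000.

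**Step 2: numerical check.** For 300 simulated household totals of widely differing size, the ratio was 1000 in every case. The SD was zero apart from floating-point error, and the difference between two groups of 150 was 0.

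**Step 3: the planned model.** Write it as

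Y(follow-up) = b0 + b1 × arm + b2 × Y(baseline) + covariates + error.

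- Y(baseline) = 1000 for everyone, so it is collinear with the intercept and b2 is not identifiable.
- Y(follow-up) = 1000 for everyone, so the fit is exact, the residual variance is 0 and the estimate of b1 is 0.
- The test statistic is 0/0, so there is no test or usable confidence interval.

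**Step 4: how far the problem extends.** Salt and saturated fat in g/MJ and expenditure in $/MJ have non-energy numerators and do vary between households; the Sample size section assumes an SD of 0.22 g/MJ for salt. That section states that "300 participants with CVD (150 per group) will provide 80% power at 5% level of significance (two-sided"), for a difference of 0.07 g/MJ. With those rounded inputs, 150 per group gives 78.7% power. With an unrounded 10% effect of 0.07125 g/MJ (0.10 × 285 mg/MJ × 2.5, taking the 285 mg/MJ to be sodium, which is an assumption) it gives 80.1%. The calculation concerns salt only and does not use the energy outcome.

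**The case against.** The strongest reply is that this is a slip in one set of brackets. The Abstract, hypotheses, Aims and Measurement sections all name energy without a per-MJ scale, for example "2) energy content of food purchases made by households", and that is a testable idea. The receipts are collected in any case, and the energy purchased has to be worked out to form the denominator of the other outcomes. The article also condenses a fuller protocol and refers to a pre-specified analysis plan, either of which may give a sensible unit.

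Much of this stands. No data are lost and the design is sound. It does not rescue the printed definition, however. Secondary outcomes is the only place where the article gives energy a unit, and following that unit yields a constant. If the analysis plan uses another unit, the two documents disagree and the article still needs correcting. The slip also has no single obvious correction, since at least two different quantities would fit the word.

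A reader might go further and infer three things that the documents do not support:

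- **That the primary outcome is compromised because energy is its denominator.** Salt in g/MJ is clearly defined and estimable. Whether an energy-adjusted endpoint is the best choice is a separate question.
- **That the plan has no means of noticing incomplete receipts or changes in the volume of shopping.** Baseline receipts are counted before randomisation, items absent from the nutrient database are recorded, and compliance is defined by shopping episodes and weekly spend per person.
- **That the analysis plan contains the same error.** It is not shown, so this is unknown.

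**Conclusion.** The point holds for one secondary outcome. As printed, energy in kJ/MJ equals 1000 for every household with E > 0, with zero variance and zero difference between arms, so the energy hypothesis and secondary aim 2 cannot be tested as specified. This follows from the unit alone and needs no assumption about the data.

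It does assume that numerator and denominator refer to the same purchases in the same period. The other outcomes in the sentence are built that way, and the article suggests no alternative. The hypothesis itself remains testable once a workable unit is stated.

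**What to change.** Before analysis, replace the kJ/MJ unit with one that can vary, define it identically at baseline and at weeks five and six, and analyse it with the same baseline-adjusted ANCOVA. Use the same definition in sub-study 2. State which quantity is intended. The two main options are:

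- **Energy purchased per household member per day.** It measures quantity bought. It can be derived from the receipts and household size, which the $25-per-member rule implies is known. It is sensitive to unreturned receipts: each missing receipt lowers the total directly, so unequal return between the unblinded arms could look like an effect.
- **Energy density, in kJ per 100 g.** It measures the composition of what is bought. Receipts that go missing regardless of their content do not shift it systematically. It needs product weights, which the article does not list among the stored data, so their availability should be confirmed first.

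The cost is about one line in the protocol and outcome list, and in the analysis plan if it carries the same unit. The first option needs no new data collection. The second needs none if product weights are already held.

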### Measurement of study outcomes

Outcome measurements for participants with CVD are undertaken in clinics at one of two locations; either the University of Auckland, or Auckland Hospital. A research assistant telephones each participant to arrange a convenient time and venue of choice for baseline, week 6, and week 12 assessments (Figure 2). Main household shoppers who do not have CVD are also encouraged to attend. On arrival at the clinic, the researcher explains procedures, answers any questions, and collects consent forms (baseline only). Height, weight, blood pressure and a urine sample are collected, and participants self-complete two on-line questionnaires. Main household shoppers who are present at clinic appointments also self-complete baseline and follow-up questionnaires; those not present are sent a link to their questionnaire in an email.

Primary outcome: the salt content of household food purchases will be assessed using supermarket till receipts linked to brand-specific food and nutrient information from the SaltSwitch app (see Intervention section). Main household shoppers are provided with a receipt collection box and return address, postage paid envelopes to return all till receipts for household food and beverages purchased during the trial. All till receipts are photographed and uploaded to a bespoke web-based data entry system that stores data on all purchased foods and beverages and their costs. The number of purchased items not included in the SaltSwitch food and nutrient database will be recorded and included in analyses.

Secondary outcomes: the saturated fat and energy content of household food purchases, and expenditure on food, will be assessed using data from till receipts, as described for the primary outcome.

Weight, height, blood pressure and urine samples are collected using standard procedures. Weight is measured on a Salter scale to the nearest 0.1 kg and height is measured on a stadiometer to the nearest cm. Blood pressure of participants with CVD (mean of three readings taken at least 3 minutes apart) is assessed seated, after 10 minutes rest, using an OMRON automatic blood pressure monitor. Participants with an average blood pressure >160/90 mmHg, with an average systolic blood pressure <90 mm/Hg, or who report dizziness when going from sitting to standing, are advised to discuss this with their General Practitioner. Prior to commencement of the trial and annually thereafter, the Salter scales and OMRON automatic blood pressure monitor were serviced and verified according to manufacturer recommendations.

Participants in sub-study 1 assessing ambulatory blood pressure are provided a calibrated Mobil-O-Graph Ambulatory 24-hour Blood Pressure Monitoring System and instructions. Sub study 1 participants are instructed to wear the monitor for one 24-hour period within the following five days and keep a diary to record events such as bed and wake-up times. Ambulatory blood pressure will be analysed using programming software for the Mobil-O-Graph.

Twenty-four hour urinary sodium excretion is considered the gold standard for measurement of sodium intake [23]. However, 24-hour urine collections carry a high participant burden and are prone to under- and over-collection and low response rates [28]. In contrast, single urinary sodium collections carry a low participant burden and may provide a reasonable estimate of the sodium intake of a group [29]. Mid-stream urine samples are collected in standard clinical urine lab containers. Five millilitres of the urine sample is transferred to a labelled, 10 mL freestanding tube and stored in a secure −4°C freezer. Frozen samples are couriered in batches to a certified laboratory and converted to predicted 24-hour urinary sodium excretion using the INTERSALT formula [30].

Data on use and acceptability of the SaltSwitch app is collected from main household shoppers via an online questionnaire. The use of the app is assessed for each week of the intervention phase using a four-point scale ranging from ‘Used every time I shopped’ to ‘Not at all’. Acceptability is assessed via three questions. The first asks how easy the app was to use on a five-point scale from ‘Very easy’ to ‘Very difficult’; the second and third are open-ended questions asking what they liked most/least about the app, and whether or not they think the app is a good way to help people with CVD to make lower-salt food choices (and why). Data on serious adverse events are collected at six and 12 weeks, regardless of causal relationship to the treatment.

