SaltSwitch is a feature of the FoodSwitch smartphone app currently available in Australia, New Zealand, and the United Kingdom, designed to help consumers make healthier food choices [19]. FoodSwitch and SaltSwitch enable users to scan the barcode of packaged foods and receive an immediate interpretive, traffic light nutrition label on screen, along with a list of healthier lower-salt alternatives to ‘switch’ to (Figure 1). The main difference between FoodSwitch and SaltSwitch is an additional criterion in the algorithm used to determine healthier options [20]. The generic FoodSwitch algorithm allocates foods with a score based on their overall nutritional profile, and the additional criterion for SaltSwitch ensures that healthier alternatives are always lower in salt than the product scanned. SaltSwitch is not yet available in New Zealand, but it is available in the UK and Australia where it has proven functionality and consumer acceptability [21].

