### Intervention

The intervention group receives the SaltSwitch smartphone app for four-weeks. SaltSwitch enables the user to scan the barcode of packaged foods and beverages using the phones camera and receive an immediate interpretive, traffic light nutrition label on screen, along with a list of healthier lower-salt alternatives to ‘switch’ to (Figure 1).

The New Zealand SaltSwitch app is underpinned by a database of ~13,000 barcodes and nutritional information for packaged foods and non-alcoholic beverages for sale in supermarkets and convenience stores [26]. Data are collected annually by fieldworkers [26]. SaltSwitch also incorporates crowd-sourcing; when a user scans the barcode of a product not already in the database, they are prompted to take three photographs (one each for the front of the pack, the nutrition information panel, and the ingredient list). Photographs are then sent to the research team and new products are subsequently added to the app.

The traffic light labels are determined using the United Kingdom’s Guidance for creating a front of pack nutrition label for pre-packaged foods [27], and healthier options are determined using the Australia New Zealand Food Standards Agency Nutrient Profiling Scoring Calculator (NPSC), a nutrient profiling model (scoring system to rank foods) used to determine whether foods are eligible to carry nutrition and health claims in Australia and New Zealand [20]. The NPSC system allocates a score to food products by balancing positive nutrients such as fibre and protein with negative nutrients including salt and saturated fat.

Main household shoppers in the intervention group are sent a link to download the SaltSwitch app to their smartphone, and are provided with a telephone tutorial. Intervention shoppers receive a reminder text message each week and are encouraged to use the app when shopping for household food and beverages.

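### The primary outcome is coded from the app's own product database, which intervention shoppers can enlarge during follow-up, so the codable share of purchases can differ by arm

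*Protocol article*

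**What the plan says.** All references are to the protocol article.

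- **Source of the outcome.** Under Measurement of study outcomes, receipts are "linked to brand-specific food and nutrient information from the SaltSwitch app (see Intervention section". Saturated fat, energy and expenditure are taken from the receipts in the same way.
- **Content of the database.** Under Intervention, the app is "underpinned by a database of ~13,000 barcodes and nutritional information for packaged foods and non-alcoholic beverages", and "Data are collected annually by fieldworkers".
- **Growth of the database.** The same section adds crowd-sourcing: "when a user scans the barcode of a product not already in the database, they are prompted to take three photographs". Then: "Photographs are then sent to the research team and new products are subsequently added to the app". No cut-off date or version is given for the copy used to code receipts.
- **Who can submit.** The download link goes to intervention shoppers (Intervention). Controls are offered the app when the trial ends (Control). Shoppers who use FoodSwitch, or plan to in the next six weeks, are ineligible (Participants). The Background states that "SaltSwitch is not yet available in New Zealand", but also that "SaltSwitch is a feature of the FoodSwitch smartphone app currently available in Australia, New Zealand, and the United Kingdom".
- **Unmatched items.** "The number of purchased items not included in the SaltSwitch food and nutrient database will be recorded and included in analyses".
- **Analysis.** ANCOVA with adjustment for the baseline measure, and no imputation of missing outcome data (Statistical analyses). Outcome assessors are not blinded (Randomisation and blinding).

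**The concern.** The outcome is a ratio, salt per MJ, computed over the purchases that the database can code. A purchase that finds no match contributes neither salt nor energy. If the app lets one arm add products to that database after randomisation, the treatment can act on the recorded outcome in two ways: through what households buy, and through which of their purchases are counted. Only the first is the effect the trial wants to estimate.

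The stated safeguards do not close the second route. A count of unmatched items shows that coverage is incomplete but supplies no salt or energy values. Baseline adjustment deals with differences that exist before allocation, whereas submissions begin after it. Because assessors know the allocation, nothing stated makes the resolution of unmatched items arm-blind. The secondary purchase outcomes expressed per MJ use the same linkage and share the exposure.

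**Working it through.** **1. The plan's own figures.** Sample size gives a difference of 0.07 g/MJ (about 10%), SD 0.22 g/MJ, 150 per group, 80% power and two-sided 5%. The source data are 285 (88) mg/MJ. The ratio 0.22/0.088 = 2.5 gives a planning mean of 0.285 × 2.5 = 0.7125 g/MJ and a 10% effect of 0.07125.

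n per arm = 2 × (1.960 + 0.842)² × (SD/difference)²

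- With 0.07125 and 0.22: 150 per arm, 300 in total, power 80.1%.
- With the rounded 0.07: 156 per arm, or 78.7% power at 150.

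The stated size reproduces, and the point does not dispute it. The figures are used only as a yardstick: mean 0.7125, target 0.07, SE = 0.22 × √(2/150) = 0.0254 g/MJ.

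**2. Model for differential coverage.** Suppose there is no true effect and the true mean is 0.7125 in both arms. Let

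- q = share of purchased energy missing from the database at the start;
- f = fraction of that share filled by submissions on intervention receipts;
- g = fraction of the same fill that control receipts also gain;
- r = salt density of missing items relative to matched ones.

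Density of matched items: m = 0.7125 / [(1 − q) + q·r]

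Observed arm mean when a fraction h is filled: obs(h) = m × [(1 − q) + h·q·r] / [(1 − q) + h·q]

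Bias = obs(f) − obs(g·f)

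The documents give none of q, f, g or r. All four are assumptions.

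**3. One case in full** (q = 0.20, f = 0.50, g = 0, r = 0.5):

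- m = 0.7125/0.90 = 0.7917
- obs(0.5) = 0.7917 × 0.85/0.90 = 0.7477
- Bias = 0.7477 − 0.7917 = −0.044 g/MJ, which is 63% of 0.07.

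**4. Range.** A negative sign favours the app. The last column but one is the chance of a significant result in either direction with no true effect (normal approximation, SE 0.0254).

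| q | f | r | Bias, controls gain none | % of 0.07 | Type I error | Bias, controls gain half |
|---|---|---|---|---|---|---|
| 0.05 | 0.10 | 0.5 | −0.0019 | 2.7 | 5.1% | −0.0010 |
| 0.05 | 0.10 | 1.5 | +0.0018 | 2.6 | 5.1% | +0.0009 |
| 0.10 | 0.25 | 0.5 | −0.0101 | 14.5 | 6.8% | −0.0050 |
| 0.10 | 0.25 | 1.5 | +0.0092 | 13.1 | 6.5% | +0.0045 |
| 0.20 | 0.50 | 0.5 | −0.0440 | 62.8 | 41.0% | −0.0207 |
| 0.20 | 0.50 | 1.5 | +0.0360 | 51.4 | 29.4% | +0.0169 |

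With r = 1 the bias is zero whatever the coverage. An extreme case (q = 0.30, f = 0.50, controls gain none) gives −0.074 (r = 0.5) or +0.055 (r = 1.5). I treat that as an outer bound, not an expectation.

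**The case against.** - **One database serves both arms.** A product added after an intervention scan can also be matched on a control receipt if linkage comes later. This stands. A reader might infer that missing products bought by controls simply stay uncoded and that ascertainment therefore does differ. The documents do not show that. What remains is that additions are selected by what intervention shoppers scan, so the benefit need not be equal. In the table, letting controls gain half the fill roughly halves the bias.
- **The timing of baseline coding is not stated.** Receipts are photographed and stored, so a single linkage run at the end is possible. Baseline receipts would then gain the added products too, and ANCOVA could absorb part of any imbalance. This stands, so it would be wrong to say that baseline adjustment cannot help. It may not help fully, because submissions follow what is scanned in weeks three to six.
- **Other sources feed the database.** Fieldworkers collect data annually, and the article does not say whether public FoodSwitch users contribute to the same database. Exclusive submission by intervention shoppers therefore holds only among trial households. The other sources are not tied to arm and do not cancel the route that is.
- **Scanning is not buying.** A submitted product need not appear on any receipt. That limits the effect without removing it.
- **Including the unmatched count in the analyses may mean only reporting it.** That is a fair reading. Using it as a model covariate is one possible reading, not the stated plan.
- **The lock date may be in the analysis plan, which is not shown.** It may well be, and silence on it in an article is no fault. The point rests on what is stated: the outcome is coded from the app's data, and the intervention can enlarge those data.

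**Conclusion.** The point holds as a risk built into the stated design: the intervention can alter the instrument that measures its own primary outcome. It is not shown that ascertainment will differ between arms, nor in which direction a difference would push the result.

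Under assumed values, the spurious difference runs from about 3% of the 0.07 g/MJ target (5% of energy missing, one tenth of it filled) to about 60% (20% missing, half filled). Type I error runs correspondingly from 5.1% to 29–41%. These figures assume that missing items have half or one and a half times the salt density of matched ones and that controls gain nothing. The bias shrinks as controls share the additions and vanishes when densities are equal. Since the sign is unknown, it could create an apparent benefit or hide a real one.

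**What to change.** Before outcome coding, specify the following.

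1. Link all receipts, from both arms and all periods, in one run by staff blind to arm, against a single locked database version.
2. For the primary analysis choose one of two versions: (a) one without products added through trial participants' submissions; or (b) one in which unmatched receipt items are resolved by the same arm-blind rule in both arms. Run the other as a sensitivity analysis. Do not rely on category values alone, because they blur the differences between brands that the app is meant to exploit.
3. Report the matched share of items and of spend by arm and period.
4. State what including the unmatched count in the analyses means, and do not adjust the primary model for that post-randomisation count.

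The cost is wording in the protocol and analysis plan, a database snapshot, and either the loss of some brand-specific values under (a) or some extra coding under (b). The app can keep its crowd-sourced updates for users. If the analysis plan already fixes these points, confirming that is enough.
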